In Uganda, a low-income country, the rural prevalence among adults aged 30 years or older, of T2DM is about 7% and of pre-diabetes is 20% [Mayega et al. 2013]. However, diagnostic facilities for T2D are available only at the higher health centres starting at health center level IV (Health Centre IV serves population of approximately 100,000 people), with almost no diagnostic and care capacity for T2D below this level [Mayega 2014]. The increase in number of diabetes cases, and the skewed distribution of care and diagnostic facilities, will over-burden the system; draining the few functioning centres, while leaving an even larger section of the population without adequate access [IDF 2015; Mbanya et al. 2010]. Moreover, those at high risk for T2DM are largely ignored because of low capacity [Mayega 2014].

*Need for community participation*

There is convincing evidence that lifestyle interventions can prevent or at least delay the onset of diabetes in individuals with pre-diabetes [Eriksson et al. 1991; Tuomilehto et al. 2001; Pan et al. 1997] and delay the onset of complications in those with T2DM. The value of delaying or preventing the development of T2DM can be seen from a societal as well as from the perspective of the individual's health and quality of life. However, this requires more than a bio-medical approach to the problem. A multidisciplinary approach focusing at an individual in terms of his or her family, community and environment and their inter-linkages and inter-dependencies is more relevant. This is in sharp contrast with the medical approach where people with an illness (like diabetes or those living with HIV or AIDS) were considered ‘patients’ dependent on medical providers [van Olmen et al. 2012]. Approaches that include community or outreach components to reach those who are not accessing the health system for one reason or other would therefore be very appropriate. However, this becomes a challenge with the current structure of the Swedish health care system, where patients are customers and the concept of catchment area for each primary care centre is no longer valid. It is therefore imperative that more innovative approaches are tried to expand the health system beyond its formal boundaries and link it to those in need.

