# 3.0 DESIGN AND METHODS

## 3.1 Study Design:

A stratified cluster-randomized trial design will be used. At each of the study sites, the clusters will be the catchment areas of participating health facilities. The health facility clusters will be randomized to either the facility alone arm, or the facility + community arm. Thus each health facility to participate in the trial, together with the community in its catchment area will be the units of randomization. Although the clusters will be the units of randomization, the enrolled individual participants will be the primary study units of measurement.

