### 3.4.1 Uganda:

In Uganda, the trial will be conducted within the two districts of Iganga and Mayuge that host the Iganga-Mayuge Health & Demographic Surveillance Site (IMHDSS). The two districts are adjacent to each other and are located in eastern Uganda approximately 120 kilometers east of Kampala along the Kampala-Kenya Highway.

Briefly, Uganda implements a level based health care system. Health Centre level I (HC I) is the lowest level of health care serving at village level to approximately 1,000 people, and has no physical structure but is a team of community health workers (CHW). Health Centre level II (HC II) is at parish level serving approximately 5,000 people. It is headed by an enrolled nurse and has approximately 3 established staff. HC II implements the “minimum activity package” including treatment of common diseases (malaria, diarrhea, skin infections, etc), integrated preventive outreaches, immunization, antenatal care and referral. It is therefore possible to provide general health education on diabetes and non-communicable diseases at this level as well as basic messages on diet, physical activity and risky habits like smoking and harmful use of alcohol. Health Centre level II (HC III) is an intermediate referral level serving about 20,000 people at sub-county level, with additional services including normal deliveries, limited in-patient care and TB treatment. It is headed by a Clinical Officer and has a laboratory that conducts basic tests (malaria, urine, blood sugar and TB). At this level, it is possible in theory but not in practice to provide blood sugar tests for individuals with proximal risk factors and refer them for follow-up care. Health Centre level IV (HC IV) is mini-hospital referral unit serving about 100,000 people in a zone called a Health Sub-district, usually covering a county. They are headed by a medical officer and have nursing officers with diverse skills. HC IVs are supposed to provide comprehensive referral services as well as support to the lower health units in their catchment zone (county). At this level, it is possible to provide pragmatic follow-up programs for high risk groups identified through targeted screening and to coordinate and NCD prevention program for this health service zone. HC V is a district hospital, HC VI regional hospital, whereas HC VII the National Referral Hospital.

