***Uganda health facilities to participate in the trial***

Only government owned public health facilities at level III to level V in Iganga and Mayuge Districts will participate in the trial. There are 4 HC IV and 19 HC III. The four HC IVs will all participate in the study, whereas 5 of the 19 HC III’s were selected to participate in the study, two from Mayuge District and 3 from Iganga District. The HC III facilities were selected such that they are reasonably far apart from each other, allowing for sufficient buffer zones between all participating health facilities to minimize chances of contamination between the trial arms. Table 9 gives the list of the selected health facilities, whereas Figure 9 shows the geographical location of the selected health facilities within the study area.

Table 9: Health facilities selected to participate in the trial

| **#** | **Name** | **Level** | **Sub-county** | **County** | **District** |
| --- | --- | --- | --- | --- | --- |
| **Iganga District** | | | | | |
| 1 | Lubira HC | III | Buyanga | Bugweri | Iganga |
| 2 | Busesa HC | IV | Ibalanku | Bugweri | Iganga |
| 3 | Bugono HC | IV | Nabitende | Kigulu North | Iganga |
| 4 | Namungalwe HC | III | Namungalwe | Kigulu North | Iganga |
| 5 | Busowobi HC | III | Nakigo | Kigulu South | Iganga |
| **Mayuge District** | | | | | |
| 6 | Kigandalo HC | IV | Kigandalo | Bunya East | Mayuge |
| 7 | Kityerera HC | IV | Kityerera | Bunya South | Mayuge |
| 8 | Baitambogwe HC | III | Baitambogwe | Bunya West | Mayuge |
| 9 | Mayuge HC | III | Mayuge Town Council | Bunya West | Mayuge |

Figure 9: Location of health facilities in Uganda selected to participate in the trial

[figure not shown]

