***South Africal health facilities to participate in the trial***

In South Africa, chronic care is offered at primary health care (PHC) facilities. In Khayelitsha PHC services are provided at 14 facilities but only 7 offer chronic care services (Table 10). These facilities are governed by 2 administrative authorities. Governed by the Provincial Government and Local Municipality (City of Cape Town)

Table 10: Facilities offering services to patients with chronic conditions

| **Name of Facility** | **Area** | **Administrative Authority** |
| --- | --- | --- |
| Khayelitsha Day Hospital/CHC | Site B | Provincial Department |
| Nolungile Day Hospital/CHC | Site C | Provincial Department |
| Michael Mapongwana Day Hospital/CHC | Harare | Provincial Department |
| Luvuyo Clinic | Makhaza | Local Authority |
| Kuyasa Clinic | Kuyasa | Local Authority |
| Matthew Goniwe Clinic | Makhaza | Local Authority |
| Town 2 Clinic | Town 2 | Local Authority |

Figure 10 shows the distribution of facilities offering services for chronic conditions that will participate in the study.

Figure 10: Location of health facilities in Khayelitsha, Cape Town, selected to participate in the trial

For the SMART2D intervention, only health facilities attached to a non-governmental organization utilizing CHWs will participate in the trial.

The SMART2D study sites will be 2 or four neighborhoods based on the facility that will be selected.

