## 3.8 Follow-up evaluations:

Each participant will be followed up to 12 months from the time of enrollment, or until his/her death or loss to follow-up. Active data collection will occur at baseline and months 3, 6 and 12. However participants with diabetes will return to their respective cluster health facilities monthly for their clinic visits and drug refills.

During follow-up study visits, we will conduct the following assessments:

1. Medical history assessment
2. Clinical evaluation of participants to assess any changes in clinical participants markers and outcomes
3. Physical measurements (weight, waist circumference and blood pressure),
4. Biochemical measurements including HbA1c and FPG (Uganda & South Africa only)
5. 7-day pedometer steps assessment
6. Participant diabetes knowledge
7. Illness perception
8. Social support and sources of support
9. Self-efficacy, autonomy support & self-regulation
10. Psychological adjustment
11. Quality of life & Stress
12. Diabetes treatment satisfaction
13. Adherence to study procedures and to intervention elements
14. Out of pocket expenditure and incremental cost on the system
15. Incremental cost to the health facility
16. Process evaluation

***Process Evaluation***: In any trial, a high degree of compliance to the intervention elements is necessary to minimize decrease in statistical power and obtain unbiased results. In the case of non-compliance that is associated with both intervention element(s) and the study outcomes of interest, there is a particularly serious threat to validity. However, the best method for ensuring full compliance is to monitor compliance with the trial processes. Thus, participants will receive encouragement at their monthly visits to take their medications at the same time every day, and identify a Care Companion to provide medication reminders, as well as healthy lifestyle adherence. Research nurses will assess compliance in three ways: direct questioning and pill count assessed at each monthly visit, and biochemical assessment of plasma glucose. Research nurses will also make an effort to identify and address barriers to compliance.

Table 15 summarizes the schedule of study procedures and tools to be applied.

Table 15: Schedule of study procedures

| **Study Activity** | | **-7 to 0 days** | **BASELINE** | **M3** | **M6** | **M12** |
| --- | --- | --- | --- | --- | --- | --- |
| **I. Consent forms** | Screening consent | X |  |  |  |  |

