$\mu_{0}$ = mean value of outcome variable (HbA1c) at month 12 in the comparison (control) arm

$\left( \mu_{0}-\mu_{1} \right)$ = minimum effect size to be detected

[figure not shown]

[figure not shown]

The necessary sample size for a cluster randomized trial depends on the variation in the intervention effects between the arms, and the clustering due to trial arm allocation (which reduces the variance of the difference between the arms), and the correlation between the repeated observations in each participant. Given that we have a fixed number of health facilities (clusters), to adjust for clustering we used a formula for fixed number of clusters and fixed number of participants within clusters as described in Hemming et al (2011) page 19 [Hemming et al. 2011].

$$Sample size per cluster=\frac{n_{i}*k*\left( 1-\rho\right)}{\left( k-n_{i}*\rho\right)}$$

where: $n_{i}$ = initial sample size

$k$ = number of clusters

= inter-cluster correlation

[figure not shown]

[figure not shown]

It is important to note that each site will be using different numbers of clusters; specifically Uganda will be working in 9 clusters, Sweden in 4 clusters, whereas South Africa will be working in 2 clusters. Thus different inter-cluster correlation (ICC) coefficient values are expected. We were unable to find published literature providing estimates for ICC coefficients for HbA1c among persons with pre-diabetes. We therefore explored various values of ICC coefficients for each site, and used values that provided the highest sample sizes to detect the desired effect size. For Uganda we used an ICC value of 0.200 to obtain a sample size of 112 participants, for South Africa we used an ICC value of 0.044 to obtain a sample size of 129, whereas for Sweden we used an ICC value of 0.06 to obtain a sample size of 79; all per study arm. For Sweden, there will be a further interest to compare the primary outcome of interest between immigrant participants of non-European origin versus immigrant participants of European origin. In order to allow for this sub-analysis, the sample size of 79 for Sweden was doubled to 158 to enable detection of the same effect size between immigrant participants of non-European origin versus immigrant participants of European origin.

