## 3.13 Statistical analysis Plan

### 3.13.1 Primary intervention efficacy analysis:

We will use intention-to-treat analyses for all primary outcomes, that is, all participants will be analyzed as assigned to their respective study arms. Since the unit of analysis for the primary outcome of interest are the individual participants, to minimize the effect of within cluster correlations, we will employ generalized estimating equations (GEEs) to evaluate changes over time in HbA1c values as a continuous variable among participants with pre-diabetes; and the proportion of participants with stabilized plasma glucose among participants with diabetes, in relation to assigned trial arm. Thus we use multivariable linear regression mixed effects modeling with a random intercept, unstructured correlation matrix and robust standard errors, to evaluate changes over time in HbA1c, and logistic regression analysis to compare the proportion of participants with stabilized plasma glucose among participants with diabetes.

Missing data are expected due to missed appointments, drop-outs, loss-to-follow-up and/or death. One technique to deal with missing data when the outcome is continuous, is hierarchical linear modeling (HLM; also called random effects regression) [Singer et al. 2003].

We do not anticipate differences in the intercept within each site, as randomization is expected to balance out baseline differences between the groups. However, there may be differences in the intercepts between sites, reflecting differences within the client populations in each site. We anticipate that the primary factor affecting the slope (i.e., the rate of change of the outcome measure) will be group membership (i.e, facility only or facility plus community intervention). If there is any significant unexplained variance after baseline differences and site membership have been accounted for, we can look for other factors influencing the slope, such as sex, age, co-morbidities, etc. Another analytic option that will be considered is generalized estimating equations (GEE) [Zeger et al. 1986], which can adjust for clustered, serially correlated data with missing values. The choice of techniques will be based on the nature of the data.

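### Facility level is not named as a stratum in Uganda, and within-site balance cannot be expected with about three clusters per arm there or one per arm in South Africa

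*Protocol*

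**What the plan says.** Protocol 3.1 states: "A stratified cluster-randomized trial design will be used". Neither that section nor 3.4 or 3.6 names the factor. Section 3.6 says only that the facility clusters are randomised before the trial starts.

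On the number of clusters, 3.10 says: "specifically Uganda will be working in 9 clusters, Sweden in 4 clusters, whereas South Africa will be working in 2 clusters". For Uganda, the subsection on participating facilities says: "The four HC IVs will all participate in the study, whereas 5 of the 19 HC III’s were selected". Table 9 confirms four at level IV and five at level III. Section 3.2 gives Uganda three arms, the third being current practice.

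The protocol also describes how the levels differ. Section 1.1 places type 2 diabetes diagnostics at HC IV and above, "with almost no diagnostic and care capacity for T2D below this level". Section 3.4.1 says of HC III: "At this level, it is possible in theory but not in practice to provide blood sugar tests". It puts a clinical officer in charge at HC III and a medical officer at HC IV. Section 3.8 says that "participants with diabetes will return to their respective cluster health facilities monthly for their clinic visits and drug refills", without distinguishing arms.

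Section 3.13.1 then sets the expectation for the analysis: "We do not anticipate differences in the intercept within each site, as randomization is expected to balance out baseline differences between the groups". It allows for baseline differences and country site, and lists sex, age and co-morbidities as further factors to explore. Facility level is not mentioned.

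**The concern.** Randomisation balances arms on average over many units. Here the units are facilities, and each site has very few. In Uganda they are of two kinds that, on the protocol's own account, start from different diabetes care. If level is not controlled in the allocation, one arm can receive most of the HC IVs and another none.

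The current-practice arm is the most exposed, because its content is whatever its facilities already do. An arm made up only of HC IIIs would represent practically no diabetes service, while one made up only of HC IVs would represent some. HbA1c and retention in care both fall under the primary objectives (2.2.1) and could plausibly depend on this. More participants per facility would not help, since the imbalance lies between facilities. Section 3.10 also sizes the trial so that each site can be analysed separately, so within-site balance is needed and cannot be left to pooling across countries.

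**Working it through.** **Inputs.** Nine Ugandan facilities, four HC IV and five HC III (Table 9). Three arms (3.2). Three clusters per arm is an assumption: the protocol does not state it, but Figure 15 gives each Ugandan arm 265 participants. South Africa has two clusters and two arms (3.10, 3.2).

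**Number of equal allocations in Uganda.** 9!/(3!·3!·3!) = 1,680. By HC IV split:

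- 2/1/1: 3 × 4!/(2!1!1!) × 5!/(1!2!2!) = 3 × 12 × 30 = 1,080 (64.3%)
- 2/2/0: 3 × 4!/(2!2!) × 5!/(1!1!3!) = 3 × 6 × 20 = 360 (21.4%)
- 3/1/0: 6 × 4 × 5!/(2!3!) = 6 × 4 × 10 = 240 (14.3%)

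Some arm has no HC IV in (360 + 240)/1,680 = 35.7%.

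**Current-practice arm.** No HC IV: C(5,3)/C(9,3) = 10/84 = 11.9%. Only HC IVs: C(4,3)/C(9,3) = 4/84 = 4.8%.

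**Difference in HC IV count between two named arms.**

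| Difference | Allocations | Unrestricted | Stratified by level (2/1/1) |
|---|---|---|---|
| 0 | 480 | 28.6% | 33.3% |
| 1 | 800 | 47.6% | 66.7% |
| 2 | 320 | 19.0% | 0 |
| 3 | 80 | 4.8% | 0 |

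A difference of two or more occurs in 400/1,680 = 23.8% of unrestricted draws and never under stratification. The standard deviation of the between-arm difference in HC IV share is √[(800×1 + 320×4 + 80×9)/(1,680×9)] = 0.43 unrestricted, and √[(2/3)×(1/9)] = 0.27 stratified.

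**Effect on a contrast.** Let D be the mean outcome difference between levels, taken as the same in both arms and with equal-sized clusters. The contrast then shifts by (difference in HC IV count)/3 × D, that is 0, D/3, 2D/3 or D. The documents give no value for D. As a yardstick only, the text of 3.10 sets 3 mmol/mol as the HbA1c difference to detect in pre-diabetes. A two-facility difference would produce a shift of that size if D were 3/(2/3) = 4.5 mmol/mol, and a three-facility difference if D were 3 mmol/mol.

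**South Africa.** Two clusters in two arms is one facility per arm, leaving 2 − 2 = 0 between-cluster degrees of freedom. Whichever facility goes to which arm, any difference between the two facilities is part of the arm contrast.

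**The case against.** **The design is called stratified, so level may be a stratum.** This stands as a limit. A reader might infer that the facilities were allocated without regard to level, but the protocol does not show that. It shows only that the factor is unnamed and that no section makes level one. The percentages therefore describe what unrestricted allocation risks, not what happened.

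**The facility-only comparator is standardised.** This also stands. Section 3.3.2.1 says that missing elements will be supplied, and 3.3.2.3 with Table 5 lists equipment, guidelines, a patient register and stock-out medicines for Uganda. The reading that the comparator's content in general depends on the draw, or that level is confounded with arm, goes too far. It applies chiefly to the current-practice arm. Between the two facility arms, what may remain is a difference in staff cadre and referral capacity.

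**The Ugandan gradient is less sharp than it looks.** Partly right. The HC III sentence in 3.4.1 concerns testing people with risk factors and referring them on. The same section gives HC III a laboratory that does blood sugar tests, and 3.3.2.3 calls Ugandan infrastructure inadequate without excepting HC IV. Section 1.1 nevertheless states a difference in both diagnostic and care capacity below HC IV.

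**The quoted sentence concerns the intercept, whereas care acts on change over time.** Fair, particularly as participants are undiagnosed or diagnosed within 12 months. But 3.13.1 goes on to expect arm to be the main influence on the slope and does not name facility level there either. In South Africa even the intercept claim has no basis with one facility per arm.

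**Covariate lists belong in the SAP.** The absent model term alone would not be a finding. The allocation rule and the stated expectation of balance are matters for the protocol.

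A reader might also infer that South African care differs by governing body, since the protocol says: "These facilities are governed by 2 administrative authorities". No section says that diabetes care differs between them, and all the listed facilities offer chronic care. Choosing facilities under the same authority would not cure one cluster per arm.

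**Conclusion.** The point holds as a material risk of chance imbalance in Uganda, not as demonstrated confounding. If allocation is unrestricted and equal at three clusters per arm, there is a 35.7% chance that some arm has no HC IV and a 23.8% chance that a given pair of arms differs by two or more. The contrasts with current practice are the most exposed. The contrast between the two facility arms is less so, because both receive the standard package. The effect on the estimates cannot be quantified, since the documents give no outcome difference between levels.

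The expectation of within-site balance in 3.13.1 is unjustified with about three clusters per arm in Uganda and cannot hold with one per arm in South Africa. The point does not extend to Sweden, where 3.6.3 allocates zones within each centre's catchment. It should be corrected, and the correction is cheap.

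**What to change.** 1. In 3.1 and 3.6, name facility level (III or IV) as the Ugandan stratum, so that the HC IV split is always 2/1/1, with the arm receiving two drawn at random.
2. Include facility level as a fixed covariate in the Ugandan primary models.
3. Replace the balance sentence in 3.13.1. Say that balance between arms within a site cannot be assumed with so few clusters, and that the South African arm contrast cannot be separated from a difference between its two facilities. Only more clusters per arm would change that.
4. If allocation is already done, add the covariate and report Ugandan outcomes by level. Reporting by level matters because the level difference may be smaller where the standard package is supplied, and a single common term would then not fully adjust the current-practice contrasts.

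**Cost.** One allocation rule, one model term and one rewritten sentence. The permissible allocations fall from 1,680 to 1,080. The covariate uses one of about six between-cluster degrees of freedom in Uganda (nine clusters less three arms). A difference of one HC IV remains in two of the three contrasts, because neither four nor five divides by three.

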## 3.10 Sample size Determination

Although the overall aim during data analysis will be to combine participants across all the three country sites, it is recognized that: a) there will most likely be baseline differences across the country sites reflecting the different population characteristics between the countries; and, b) each site will want to analyze data from their site-specific arms. Thus the sample was calculated such that differences between the trials arms in regard to primary outcomes can be detected at each study site separately when desired.

The sample size for this trial has been determined based on the primary hypothesis that by the end of follow-up, the “facility plus community” arm will be superior to the “facility alone” arm, and the current practice arm in Uganda, with respect to: a) mean HbA1c readings among participants with pre-diabetes, and b) the proportion of participants with diabetes with controlled blood sugar levels.

*Sample size for participants with pre-diabetes*

With the aim of being able to detect an average difference between any two trial arms, in mean HbA1c by month 12 of at least 3 mmol/mol (effect size), with a standard deviation of 2.5 mmol/mol in the intervention arm, and a standard deviation of 2.5 mmol/mol in the comparison (control) arm; the required sample size before adjusting for clustering, at an 80% power and 5% level of significance is 34 participants per arm. For this first stage calculations, we used the formula as described in Hayes and Bennett (1999) [Hayes et al. 1999] for a continuous outcome:

$$Initial sample size(n_{i})=\left[ \frac{\left( Z_{\alpha/2}+Z_{\beta} \right)^{2}*\left( \sigma_{0}^{2}+\sigma_{1}^{2} \right)}{\left( \mu_{0}-\mu_{1} \right)^{2}} \right]$$

where: $Z_{\alpha/2}$ = standard normal distribution value at $\alpha$ level of significance

= standard normal distribution value at level of significance

[figure not shown]

[figure not shown]

[figure not shown]

[figure not shown]

$\alpha$ = level of significance

= type 2 error, for which (1-$\beta$) is the power of the study to detect the desired effect size

[figure not shown]

[figure not shown]

$\sigma_{0}^{2}$ = variance of outcome variable (HbA1c) at month 12 in the comparison (control) arm

$\sigma_{1}^{2}$ = variance of outcome variable (HbA1c) at month 12 in the intervention arm

$\mu_{1}$ = mean value of outcome variable (HbA1c) at month 12 in the intervention arm

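### Section 3.13.1 contradicts itself on the primary model and leaves the technique and covariates to be chosen from the data, with no criterion and no blinding to arm

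*Protocol*

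**What the plan says.** Section 3.13.1 of the Protocol makes these statements about the primary analysis, in this order:

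1. GEE will be used, for HbA1c in pre-diabetes and for the responder proportion in diabetes.
2. "Thus we use multivariable linear regression mixed effects modeling with a random intercept, unstructured correlation matrix and robust standard errors" are then specified for HbA1c, with logistic regression for the responder proportion. The level of the random intercept (facility or participant) and of the robust standard errors is not given.
3. Hierarchical linear modelling is named as one technique for missing continuous outcomes, and the text equates it with random effects regression.
4. If significant variance remains after baseline and site are accounted for, "we can look for other factors influencing the slope, such as sex, age, co-morbidities, etc".
5. "Another analytic option that will be considered is generalized estimating equations (GEE").
6. "The choice of techniques will be based on the nature of the data".

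The text that follows makes pooling across countries, or falling back to site-specific comparisons, depend on what the data show. Section 3.10 sizes the trial for a single test: "at an 80% power and 5% level of significance is 34 participants per arm".

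**The concern.** Statements 1 and 5 conflict: GEE is first the method and then a possibility. Statement 2 is worded as though a mixed model followed from GEE, but the two are different analyses. Statement 6 then settles the matter by a rule, and the rule is the data. A protocol may stay silent here and defer to a SAP. This one instead prescribes a data-driven choice of the primary test, so a SAP that fixed one model would contradict it.

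Two things are at stake. If arm effects are visible when the technique and covariates are chosen, the reported p-value is one of several and no longer has its nominal level. And with so few clusters the candidate tests have different true levels, so the one picked affects the result even if nobody selects on significance.

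**Working it through.** **The plan's own figure.** The 5% level is a design input. The sample size attached to it does not reproduce. Section 3.10 takes a difference "in mean HbA1c by month 12 of at least 3 mmol/mol (effect size"), "with a standard deviation of 2.5 mmol/mol in the intervention arm" and the same in the control arm. With (1.96 + 0.8416)² = 7.849, n = 7.849 × (6.25 + 6.25) / 9 = 10.9, so 11 per arm. The 5 mmol/mol printed in Table 16(a) gives 7.849 × 12.5 / 25 = 3.9, so 4. A figure of 34 needs a difference of √(7.849 × 12.5 / 34) ≈ 1.7 mmol/mol. That is a separate defect, and nothing below rests on it.

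**Candidate techniques.** Hierarchical linear modelling and the mixed model are one family by the Protocol's own description. That leaves two techniques, mixed model and GEE, multiplied by an open set of covariates.

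**Clusters per arm.** Section 3.10 gives 9 clusters in Uganda, 4 in Sweden and 2 in South Africa. With equal allocation (Uganda over three arms), the facility-plus-community versus facility-only contrast has 3 + 2 + 1 = 6 clusters per arm.

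**Level of each single test, nothing selected.** Take equal clusters, a continuous outcome, no covariates and k clusters per arm. The model-based variance uses divisor k(k − 1) and the sandwich variance uses k². The sandwich standard error is therefore √((k − 1)/k) times the model-based one. Both are referred to the normal value 1.96, although the statistic follows t with 2(k − 1) degrees of freedom.

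- k = 6, model-based: P(|t₁₀| > 1.96) = 7.8%.
- k = 6, sandwich: 1.96 × √(5/6) = 1.789, and P(|t₁₀| > 1.789) = 10.4%.
- k = 3 (Uganda alone), model-based: P(|t₄| > 1.96) = 12.2%.
- k = 3, sandwich: 1.96 × √(2/3) = 1.600, and P(|t₄| > 1.600) = 18.5%.

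**Simulations under the null.** Simulation A used cluster means, 6 versus 6 clusters of 73 participants ((124 + 142 + 174)/6 from Table 16(a)), ICC 0.02-0.20 and 8,000 runs per ICC. Simulation B used individual data, 3 + 1 + 2 clusters per arm, the stated sizes and ICCs, SD 2.5, 2,000 runs per scenario, and three covariate sets (site; plus baseline; plus age, sex and comorbidity).

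| Nominal 5% | Mixed, model-based SE | GEE, sandwich SE | Smaller p of the two | Best over models and covariate sets |
|---|---|---|---|---|
| A, pooled | 7.1-8.0% | 9.8-10.4% | – | 11.7-14.0% (four) |
| B, pooled, stated ICCs | 6.8-7.2% | 14.4-14.7% | 14.6% | 16.4% (six) |
| B, pooled, ICCs quartered | 6.8% | 16.2-16.6% | 16.6% | 20.0% (six) |
| B, Uganda alone | 11.8-12.6% | 18.4-18.6% | 18.6% | 20.6% (six) |

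Taking the smaller p of the two techniques adds nothing to the sandwich test on its own. Most of the excess over 5% in the last column is therefore few-cluster miscalibration, not selection.

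**Selection alone.** In B, each model was first calibrated to exactly 5%:

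- smaller p of mixed model and GEE: 5.3-5.9%;
- best of three covariate sets in the mixed model: 6.2-6.6%;
- best of all six: 6.6-8.0%;
- a pick unrelated to the arm effect: 4.8-5.2%.

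In a further 4,000 runs, an exact cluster-level t-test with true size 4.8% rose to 9.8% (ICC 0.02) and 8.0% (ICC 0.055) when the smallest p over all 8 subsets of three covariates was taken. Each covariate was assumed to correlate 0.15 with the outcome and to have an ICC of 0.10.

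**The case against.** The strongest reply is that the section does not select on significance. Its closing sentence follows one about clustering, serial correlation and missing values, and could mean that the method will be matched to data structure. A choice unrelated to the arm effect holds its level, as shown above. That stands, and it makes the inflation conditional. But the Protocol states no such restriction.

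A second reply also stands in part. The mixed model in the Protocol carries robust standard errors. If both the intercept and those errors are at facility level, in a balanced linear design it coincides with exchangeable GEE and shares its level. The 7-8% applies only to model-based standard errors. Which version is meant cannot be told from the text.

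A third reply is that looking for other factors on the slope may be meant as explanation rather than as redefining the primary test, and that a final covariate list can sit in the SAP. That is possible, but the sentence stands in the primary analysis section without that label.

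Stronger readings that a reader might infer are not supported:

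- That the open choice by itself produces a 12-20% test. Most of that comes from Wald tests with few clusters.
- That two analysts would reach opposite conclusions. Nothing calculated here shows it.
- That GEE is necessarily biased under the expected dropout. Table 15 schedules HbA1c only at baseline and month 12. At the projected 10% loss, with baseline-dependent dropout running in opposite directions by arm, bias was about 1% or less with baseline as a covariate or a correlated working structure. It was material only for unadjusted or independence-type analyses.
- That the two responder odds ratios differ importantly. At ICC 0.02-0.091 and an assumed 30% response, the log odds ratios differ by about 1-8%, and both test the same null.

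**Conclusion.** The point holds. The primary model is stated inconsistently, and the stated rule for resolving it is the data, for technique and covariates alike. Selection made with arm results visible costs about 0.3-3 percentage points on a calibrated 5% test, or up to about 5 points if the smallest p over covariate subsets is taken. Selection made blind to arm costs essentially nothing. Separately, the few clusters put the pooled candidates at about 7-8% (model-based) and 10-15% (sandwich, slightly more if the ICCs are a quarter of those stated). Naming a model without correcting its reference distribution would therefore still not give 5%.

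These sizes rest on assumptions the Protocol does not supply: three Ugandan clusters per arm, equal cluster sizes, normal cluster effects, modest covariate effects and analysis of month 12 only. The logistic responder endpoint was not simulated. The contradiction in the text depends on none of them.

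**What to change.** Before unblinded data are seen, name one primary analysis per endpoint in Section 3.13.1:

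- HbA1c in pre-diabetes: a linear mixed model with a facility random intercept.
- Responder status in diabetes: one named logistic model that accounts for facility.
- Both: a fixed covariate list, for example arm, country, baseline HbA1c, age and sex.
- Both: a small-sample reference suited to the endpoint, for example Kenward-Roger or Satterthwaite degrees of freedom, or a t-test on cluster summaries.

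Delete the closing sentence on the choice of techniques. Label GEE and any further covariates as sensitivity analyses. State the rule for pooling across countries in the same edit.

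The cost is protocol or SAP wording, the loss of post-hoc flexibility, and slightly wider intervals from the small-sample reference.
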